### Sample size for randomized fast-track trial phase

The sample size required per group to detect at least a minimal clinically important mean difference of 20 % (SD ±25) in arm lymphedema volume in favor of either the standard care + NCSG, standard care + CB group and standard care alone is 36 participants. A total sample of 108 participants will achieve a power of 86 % with a significance level of 0.05 using a one way ANOVA test. The sample size required per group to detect at least a minimal clinically important difference on the Lymph-ICF quality of life scale of 15 points out of 100 (SD ±22) between the standard care + CB group and the standard care + NCSG group is 36 participants. A total sample of 108 will achieve a power of 80 % with a significance level of 0.05 using a two-sided Mann-Whitney test assuming the actual distribution is normal. To allow for an estimated 10 % loss to follow-up and non-compliance/cross-over of the standard care group, we will recruit an additional 12 patients for a total of 120 participants (40 participants in each of the three treatment groups).

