### Hypotheses of randomized controlled trial (Phase I)

Standard care plus the addition of CB will provide statistically significant improved management of **arm lymphedema volume** compared to standard care alone at 12-weeks.Standard care plus the addition of NCSG will provide statistically significant improved management of **arm lymphedema volume** compared to standard care alone at 12-weeks.Standard care plus the addition of NCSG will provide statistically significant benefit in **quality of life**, **sleep and self**-**efficacy** over standard care plus CB and standard care alone at 12-weeks.

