### Allocation concealment and method of randomization

Participants will be randomized in a 1:1:1 ratio to Standard Care, CB or NCSG using a secure central randomization service administered by the Clinical Trials Unit of the Cross Cancer Institute.

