### Statistical analyses

Baseline medical and demographic characteristics, arm dominance relative to the lymphadematous arm, and adverse events of the three groups will be compared using one-way ANOVA for continuous data and Pearson’s Chi-square tests for categorical data. The primary analysis will compare the groups with regard to percent excess lymphedema volume and quality of life at 12-weeks using a one-way ANOVA. General linear models will be used to adjust for centre and lymphedema category (mild or moderate), and to evaluate the treatment effect in subgroups defined by the strata. Sleep quality, self-efficacy, and adherence-related outcomes will be analyzed by repeated measures modeling and one-way ANOVA on change scores.

Descriptive data on accrual rates will include the number of women screened for eligibility, the number eligible, the number agreeing to participate, and reasons for refusal to participate. Data on adherence will be collected from all women throughout the 24-week study period. Adherence data will include days worn per week and hours worn per 24-h period, as appropriate, for each of the following: 1) NCSG; 2) CB; 3) day-time compression sleeve. We will also examine adherence during weeks 13 to 24 to the newly assigned NCSG for the standard care and standard care + CB groups, and ongoing adherence during weeks 13 to 24 in the originally assigned standard care + NCSG group. Analyses of primary outcomes will be performed at the end of the RCT portion of the trial. Within group analyses will also be conducted for primary and secondary outcomes from weeks 13 to 24 following completion of all follow-up measures.

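### Hypotheses 1 and 2 each compare one night-time arm with standard care on arm volume, but the stated primary test and its 86% power belong to a three-group F-test that decides neither

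*Protocol article*

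**What the plan says.** In the protocol article, the section on hypotheses of the randomized phase makes two distinct claims about arm volume. The first begins "Standard care plus the addition of CB will provide statistically significant improved management of" and the second "Standard care plus the addition of NCSG will provide statistically significant improved management of". Both take the same comparator and time point: "compared to standard care alone at 12-weeks".

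The sample size section sets a "minimal clinically important mean difference of 20 % (SD ±25) in arm lymphedema volume". It then says "A total sample of 108 participants will achieve a power of 86" per cent, "with a significance level of 0.05 using a one way ANOVA test". The sentence that sets the difference lists all three arms and singles out no pair. The quality-of-life calculation in the same section does name a pair, CB against NCSG.

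The section on statistical analyses fixes the test: "The primary analysis will compare the groups with regard to percent excess lymphedema volume and quality of life at 12-weeks using a one-way ANOVA". It adds general linear models to adjust for the two stratification factors and to look at subgroups. It names no contrast of either night-time arm with standard care, and no multiplicity rule for volume.

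**The concern.** The hypotheses ask two yes-or-no questions, each about one arm against standard care and each with a direction. The F-test with 2 and 105 degrees of freedom asks a single question without direction: are the three means all equal? Rejecting that does not say which arm differs, from what, or which way, and it gives no effect estimate. The power figure has the same limit. It is the chance of detecting some difference among three arms, so a reader cannot learn from it how likely the trial is to establish hypothesis 1 or hypothesis 2.

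At stake is the link between the primary result and the trial's two headline volume conclusions. Followed literally, the primary analysis yields one p-value for two claims.

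**Working it through.** **Inputs.** From the sample size section: difference 20, SD 25, 108 evaluable participants (36 per arm), alpha 0.05, one-way ANOVA. From the section on allocation: "Participants will be randomized in a 1:1:1 ratio to Standard Care, CB or NCSG". Assumed here: pairwise tests are two-sided, and means are expressed as benefit with standard care at 0 unless stated.

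**1. Reproduce the 86%.** Power is P(F > 3.083), where F is noncentral with 2 and 105 df and noncentrality λ = n Σ(μᵢ − μ̄)² / SD².

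| Means | Σ(μᵢ − μ̄)² | λ = 36 × Σ / 625 | Power |
|---|---|---|---|
| 0 / 10 / 20 | 200 | 11.52 | 85.9% |
| 0 / 15 / 20 | 216.7 | 12.48 | 88.7% |
| 0 / 20 / 20 or 0 / 0 / 20 | 266.7 | 15.36 | 94.3% |

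The stated figure therefore matches the midway pattern. The article does not state that pattern; it is inferred from the match. The enlargement to 120 also holds: 108 / 0.90 = 120.

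**2. What a significant F leaves open.** In the last row, the pattern 0 / 0 / 20 has one night-time arm no better than standard care, so one hypothesis is false, yet F rejects 94.3% of the time. F also ignores which arm is which. With standard care in the middle (CB 10 below, NCSG 10 above) its power is the same 85.9%. In simulation, F is then significant while neither contrast with standard care reaches 0.05 in about 17% of trials.

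**3. Power for the hypotheses themselves.** For one contrast the noncentrality is δ / (SD √(2/n)) = 20 / (25 × √(2/36)) = 20 / 5.893 = 3.394.

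| Two-sided alpha | Two arms only (70 df) | Pooled variance (105 df) |
|---|---|---|
| 0.05 | 91.7% | 92.0% |
| 0.025 | 86.2% | 86.7% |

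So 36 per arm gives about 86% per contrast even when alpha is halved. By the normal approximation, 35 per arm would suffice for 86%.

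**4. Two ways to control error (simulation, 400,000 runs, pooled variance).** If both night-time arms gain 20:

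| Procedure | Each hypothesis | Both |
|---|---|---|
| Pair tests at 0.05 only after a significant F | 90% | 86% |
| Holm on the two contrasts | 90% | 86% |

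With no true differences, the gated procedure makes any false pairwise claim in 5.0% of trials. At 0 / 0 / 20 it makes a false claim for the ineffective arm against standard care in 5.0%.

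**The case against.** The strongest reply is that this is a condensed article and that pairwise comparisons after an ANOVA are usually left to the analysis plan. The hypotheses already show which comparisons matter, and nothing forbids reporting them. With three arms, unadjusted pair tests run only after a significant F hold the familywise rate at 5%, and they perform as well as Holm contrasts. On this view the point is a preference.

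Much of that stands. It limits the consequence, but it does not remove the mismatch. The article is not silent on the primary test: it names one and attaches a power figure to it, and that test does not answer the two stated questions. A later pairwise step would add to the stated primary analysis.

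Two stronger readings are tempting and are not supported.

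- *That the plan inflates type I error.* Pair tests at 0.05 without the F gate would give a false claim in about 12% of trials over three pairs, or 9% over the two contrasts with standard care. The article proposes no such procedure.
- *That the trial is underpowered because the middle arm at 0 / 10 / 20 has only 39% power against standard care.* That is power for a 10-point effect, half the stated target. Low power there is expected, and naming contrasts would not raise it.

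**Conclusion.** The mismatch holds. The volume hypotheses are two comparisons with standard care. The primary analysis and its sizing use an omnibus test that decides neither, and the 86% is not the power for either. The 86% and the 120 are arithmetically right, and 36 per arm is adequate for each contrast at the stated difference (86% to 92%, depending on the alpha used). What is wrong is the stated target of the test and of the power figure. A reader might infer that the trial is too small or that its error rate is uncontrolled; the documents support neither.

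This rests on two assumptions: that the 0 / 10 / 20 pattern lies behind the 86%, and that pairwise tests would be two-sided. The first affects only the explanation of the stated figure. The point should be fixed, but it is not critical.

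**What to change.** - In the section on statistical analyses, name CB minus standard care and NCSG minus standard care at week 12 as the primary contrasts for arm volume, each with a confidence interval. The F-test can stay as a descriptive summary.
- State the familywise rule. Holm across the two contrasts at two-sided 0.05 is suitable. Pair tests gated by the F-test would also hold 5% with three arms, provided that the gate is written down.
- In the sample size section, restate the volume sentence: 36 per arm gives about 86% power for each contrast at two-sided 0.025, for a difference of 20 with SD 25. Say that this is a new calculation (86.2%, or 86.7% with pooled variance) that happens to fall close to the omnibus figure of 85.9%.

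The cost is wording only. The sample size stays at 108 evaluable and 120 recruited, and no data collection changes. The change should be made before the week-12 data are analysed by arm.

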### Statistical analyses

Baseline medical and demographic characteristics, arm dominance relative to the lymphadematous arm, and adverse events of the three groups will be compared using one-way ANOVA for continuous data and Pearson’s Chi-square tests for categorical data. The primary analysis will compare the groups with regard to percent excess lymphedema volume and quality of life at 12-weeks using a one-way ANOVA. General linear models will be used to adjust for centre and lymphedema category (mild or moderate), and to evaluate the treatment effect in subgroups defined by the strata. Sleep quality, self-efficacy, and adherence-related outcomes will be analyzed by repeated measures modeling and one-way ANOVA on change scores.

Descriptive data on accrual rates will include the number of women screened for eligibility, the number eligible, the number agreeing to participate, and reasons for refusal to participate. Data on adherence will be collected from all women throughout the 24-week study period. Adherence data will include days worn per week and hours worn per 24-h period, as appropriate, for each of the following: 1) NCSG; 2) CB; 3) day-time compression sleeve. We will also examine adherence during weeks 13 to 24 to the newly assigned NCSG for the standard care and standard care + CB groups, and ongoing adherence during weeks 13 to 24 in the originally assigned standard care + NCSG group. Analyses of primary outcomes will be performed at the end of the RCT portion of the trial. Within group analyses will also be conducted for primary and secondary outcomes from weeks 13 to 24 following completion of all follow-up measures.

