**Methods/Design:**

The study will be a parallel 3-arm, multi-centre randomized fast-track trial. A total of 120 women with breast cancer related lymphedema will be recruited from 3 centres in Canada and randomized to group 1: Day-time compression garment alone or Group 2: Day-time compression garment + night-time compression bandaging or Group 3: Day-time compression garment + use of a night-time compression system garment. The duration of the primary intervention period will be 12 weeks. The follow-up period after the intervention (weeks 13 to 24) will follow a longitudinal observational design. The primary outcome variables: differences from baseline to week 12 in arm volume and quality of life (Lymphoedema Functioning, Disability and Health Questionnaire: Lymph-ICF). Secondary outcomes include bioimpedance analysis, sleep disturbance and self-efficacy. All measurements are standardized and will be performed prior to randomization, and at weeks 6, 12, 18 and 24.

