### Participants

The following eligibility criteria will be used to determine participant inclusion in the trial:Women with a histological diagnosis of breast cancer experiencing lymphedema in the ipsilateral arm such that there is a minimum 200 ml or 10 %, and maximum 40 % increase in arm volume over the unaffected arm (indicative of mild to moderate lymphedema) [14].Survivors must have completed all primary and adjuvant cancer treatments (with the exception of hormonal treatment) by a minimum of 1 month prior to randomization.Survivors must be in or entering the lymphedema maintenance phase and agreeable to **not** pursuing any other lymphedema maintenance treatments beyond day-time use of a compression sleeve.Survivors must have their own properly fitted compression sleeve for day-time maintenance and must agree to wear their day-time sleeve as per standard care for a minimum of 12 h per day.No current use of night-time compression for maintenance. Any survivor who has trialed a NCSG/performed night-time CB in the past year for maintenance purposes must observe a one-month washout period before entering the trial.

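### The primary arm-volume endpoint is defined in three different ways, and the stated 86 % power does not carry over to the week-12 percent-excess ANOVA named as the primary analysis

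*Protocol article*

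**What the plan says.** Three sections of the protocol article describe the primary arm-volume endpoint.

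- **Abstract, Methods/Design:** "The primary outcome variables: differences from baseline to week 12 in arm volume and quality of life". This is a change score.
- **Sample size for randomized fast-track trial phase:** a "minimal clinically important mean difference of 20 % (SD ±25) in arm lymphedema volume", followed by "A total sample of 108 participants will achieve a power of 86 % with a significance level of 0.05 using a one way ANOVA test". The section does not say whether the 20 % is percentage points of excess, a relative change, or a level at week 12.
- **Statistical analyses:** the primary analysis will "compare the groups with regard to percent excess lymphedema volume and quality of life at 12-weeks", by one-way ANOVA. This is a level at one time point. General linear models adjusting for centre and for mild or moderate category come next; the baseline value is not named as a covariate. The same paragraph does specify change scores, but only for sleep, self-efficacy and adherence-related outcomes.

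The Participants section limits entry to an excess over the unaffected arm of at least 10 % or 200 ml and at most 40 %. The design section expects only a small early reduction in volume, then a plateau.

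**The concern.** A power figure is tied to one variable and one test. Here the variable that was sized has no stated scale, the variable to be tested is a week-12 level, and the abstract promises a change. A week-12 level carries all the between-woman spread present at baseline, which a change score or a baseline-adjusted analysis largely removes. If the 20 % (SD 25) is a relative change, the declared primary test has less power than the protocol reports for the difference it calls minimally important. Three definitions of one primary endpoint also leave room to choose among them once data are available.

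**Working it through.** **1. Reproduce the stated power.** Inputs from the sample-size section: three arms, 36 per arm, difference 20, SD 25, alpha 0.05, one-way ANOVA. With equally spaced means 0/10/20, the noncentrality is 36 × (10² + 0² + 10²)/25² = 36 × 200/625 = 11.52 on 2 and 105 degrees of freedom. Power is 85.9 %, matching the stated 86 %. With means 0/20/20 the noncentrality is 36 × 266.7/625 = 15.36 and power is 94.3 %. The inflation is also correct: 108/0.9 = 120.

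**2. Can 20 (SD 25) be percentage points of excess?** A variable confined to 10-40 has an SD of at most 15 (half the range), or 30/√12 = 8.7 if uniform. Week-12 values are not bound by the entry range. But if change is independent of baseline, a week-12 SD of 25 needs a 12-week change SD of at least √(25² − 15²) = 20 points, or √(25² − 8.66²) = 23.5 from a uniform baseline. A 20-point benefit would also remove most or all of the excess in a typical participant, while the protocol expects a small reduction. This reading is not credible. A relative change of 20 % (SD 25 %) in excess volume is.

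**3. What a 20 % relative change means for the week-12 level.** Let baseline percent excess have mean m and SD s, and let relative change have SD 25 % independent of baseline. The standardised difference, using the control-arm SD, is

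0.20m / √(0.0625(m² + s²) + s²).

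This equals 0.80 (that is, 20/25) only when s = 0, and any baseline spread lowers it. The direction therefore does not depend on the assumed mean or SD.

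Example, uniform on 10-40 % (m = 25, s = 8.66): the difference is 5 points and the control SD is √(0.0625 × (625 + 75) + 75) = 10.9, giving 5/10.9 = 0.46. The 20 %-reduction arm has SD 9.6, so the pooled SD is √((10.9² + 9.6²)/2), about 10.3. Noncentrality is 36 × (2.5² + 2.5²)/10.26² = 4.3 and power is 43 %. With 0/-20/-20 % it is 55 %.

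**4. Range under stated assumptions.** The documents give no mean or SD for percent excess. Assumed: baseline on about 10-40 % (uniform, or truncated normal with location 15-25 and scale 5-8; some runs extended down to 8 %), relative-change SD 25 % independent of baseline, 36 per arm, mild/moderate cut at 20 %.

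| Analysis | Arms 0/-10/-20 % | Arms 0/-20/-20 % |
|---|---|---|
| Week-12 percent excess, unadjusted ANOVA (as written) | about 35-67 % | about 51-81 % |
| Week-12 percent excess, adjusted for severity category | about 64-74 % | about 75-86 % |
| Week-12 percent excess, adjusted for its baseline value | about 80-85 % | about 91-94 % |
| Percent change from baseline | about 84-87 % | about 94 % |

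The lowest unadjusted values (35-47 %) come from runs with stratified allocation and wide baseline spread. The last row returns the stated power by construction, because the data were generated on that scale.

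**The case against.** The strongest reply is that the shortfall is not in the documents. They give no mean or SD for percent excess, and letting both vary freely (mean 15-30, SD 6-12) gives power from 14 % to 99 %. This stands against any single figure. A reader might infer that the trial has only 35-47 % power; that is one set of assumptions. The 99 % end, however, needs pairs such as mean 30 with SD 6, which a 25 % relative-change SD excludes under independence, since 0.25 × 30 is already 7.5.

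Second, the protocol plans models adjusted for centre and severity, and its hypotheses expect both night-time arms to beat standard care. Both points stand: together they bring power to about 75-86 %, so it does not follow that the trial would probably miss its target effect. But those models follow the primary ANOVA, and a two-level category recovers only part of what the baseline value would.

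Third, the relative-change reading is an inference. A reader might conclude that the 20 % must be a relative change; the text does not say so, and if it were percentage points the 86 % would apply unchanged. The 10-40 % range bounds baseline only, and the 200 ml alternative can admit women below 10 %. Even a 0-40 % range (SD at most 20) would still need a change SD of √(25² − 20²) = 15 points.

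Fourth, the week-12 wording may be loose shorthand for change, since the protocol elsewhere expresses relapse relative to baseline. That is possible, but the same paragraph names change scores for other outcomes and not for these. An unadjusted week-12 ANOVA is valid under randomisation; the issue is its power and the inconsistent definition, not bias. Nor do the simulations show that percent change is the better endpoint.

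Lastly, an article may leave endpoint derivation to a fuller document. It may, but here the text states three definitions that disagree.

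**Conclusion.** The point holds as an inconsistency in the primary endpoint with a consequence for power. The 86 % is correct arithmetic for 20 (SD 25). It does not carry over to the week-12 percent-excess ANOVA if, as is most natural, 20 (SD 25) is a relative change in excess volume. On that reading, with change independent of baseline, power for the declared test is below the stated value for any baseline spread: roughly 35-67 % with equally spaced arms and about 51-81 % if both night-time arms achieve the full effect, where the matching figure on the sized scale is 94 %. These ranges rest on assumed baseline distributions and are not facts about the trial. The documents do not support a claim that the trial is underpowered by a known amount.

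**What to change.** Choose one arm-volume variable and use it in the abstract, the sample-size section and the Statistical analyses section. Either of these would serve:

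- percent change in excess volume from baseline to week 12; or
- percent excess at week 12, adjusted for its baseline value as a continuous covariate, with centre and severity category kept in the model.

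State that 20 % (SD 25) is on the chosen scale, or convert it and give the SD of the chosen variable, and restate the power for that analysis. Treat Lymph-ICF likewise: the abstract promises a change and the analysis section a week-12 comparison, so specify change from baseline or week-12 score adjusted for baseline.

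The cost is wording and a power figure that may become slightly less favourable (about 80-85 % rather than 86 % for the baseline-adjusted analysis with equally spaced arms). Baseline values are already collected before randomization, so no new data or patients are needed. The change should be recorded before the week-12 data are analysed.

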## Methods/Design

The study will be a parallel 3-arm, multi-centre randomized fast-track trial including the Cross Cancer Institute (CCI) in Edmonton, Tom Baker Cancer Centre (TBCC) in Calgary and Mount St. Joseph’s Hospital (MSJ) in Vancouver. Women enrolled in the study will be stratified by accruing centre (CCI, TBCC, MSJ) and by lymphedema severity (i.e., mild versus moderate lymphedema as per the classification criteria of International Society of Lymphology) [9, 14], and then randomly assigned to one of three groups: (1) standard care (day-time use of a compression sleeve alone); (2) standard care plus night-time compression by self-administered or assisted CB; (3) standard care plus night-time compression by a traditional NCSG. The duration of the primary intervention period will be 12 weeks. Results from the pilot study and previous case studies suggest a small initial reduction in arm lymphedema volume from administration of the traditional strapped NCSG over the first 6 weeks with stabilization of arm volume (plateau) occurring thereafter. Thus, the 12-week intervention period is deemed sufficient to observe an intervention effect and was chosen to align with current clinical follow-up time periods. Following the 12-week intervention period, participants in the CB and standard care groups will be measured for a NCSG. Participants in these two groups will follow the protocol as per the NCSG group during weeks 13 to 24 [Fig. 3].

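### The primary test is an unadjusted week-12 one-way ANOVA, although allocation is stratified and baseline values are collected; this forgoes precision and leaves open which model leads

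*Protocol article*

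**What the plan says.** Four statements in the protocol article bear on this point.

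- **Primary test** (Statistical analyses): "The primary analysis will compare the groups with regard to percent excess lymphedema volume and quality of life at 12-weeks using a one-way ANOVA". No covariate is named.
- **Adjusted models** (same section, running on from the ANOVA): "quality of life at 12-weeks using a one-way ANOVA. General linear models will be used to adjust for centre and lymphedema category". The same models are also meant to look at treatment effects within strata. The text does not say whether these models are primary, supportive or only for subgroups. The baseline value of the outcome is not among the terms listed.
- **Allocation** (Methods/Design): "Women enrolled in the study will be stratified by accruing centre (CCI, TBCC, MSJ) and by lymphedema severity". That gives 3 × 2 = 6 strata. Severity is mild or moderate, so it is a coarse category of baseline excess volume.
- **Outcome definition and visits** (Abstract, Methods/Design): "The primary outcome variables: differences from baseline to week 12 in arm volume and quality of life". Measurements "will be performed prior to randomization, and at weeks 6, 12, 18 and 24".

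Repeated-measures models and change scores do appear in the Statistical analyses section, but only for other outcomes: "Sleep quality, self-efficacy, and adherence-related outcomes will be analyzed by repeated measures modeling and one-way ANOVA on change scores".

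**The concern.** Stratified randomization balances the groups on centre and severity. If those factors predict the week-12 value, the true sampling variance of a group difference no longer contains the between-strata part. The one-way ANOVA still leaves that part in its error term, so its standard error is too large and it rejects too rarely under the null.

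The baseline value raises a related but separate issue. Apart from what severity captures, it is not balanced by design, so leaving it out does not invalidate the test. It only leaves explainable variance in the error term and widens the confidence intervals.

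There is also an ambiguity. The article supports three analyses of each primary outcome: an unadjusted week-12 comparison, a model adjusted for the strata, and a change from baseline. These can give different p-values, and a choice among them after the data are seen would weaken the primary result.

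**Working it through.** **Inputs from the article.** 36 women per group (N = 108), 1:1:1 allocation, significance level 0.05. Arm volume: difference 20, SD 25, stated power 86%. Lymph-ICF: difference 15, SD 22, stated power 80% for a pairwise Mann-Whitney test.

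**Inputs assumed, because the article gives no value.** Baseline to week-12 correlation ρ from 0.3 to 0.7, and share R² of week-12 variance explained by the six strata from 0.05 to 0.30.

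**1. Reproduce the stated power.** For a three-group one-way ANOVA the noncentrality is λ = n Σ(μᵢ − μ̄)² / SD², with 2 and 105 degrees of freedom. With means 0/10/20:

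λ = 36 × (100 + 0 + 100) / 625 = 11.52, critical F = 3.083, power = 85.9%.

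This matches the stated 86%. For Lymph-ICF, a two-sided t-test with Mann-Whitney efficiency 0.955 gives 79.6%, which matches 80%. The loss allowance also reproduces: 108 / 0.9 = 120. So the stated power is already that of the unadjusted test.

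**2. Type I error of the unadjusted ANOVA after stratified allocation.** With exact balance in six strata, the model standard error exceeds the true one by about 1/√(1 − R²). Simulation under the null:

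| R² of strata | SE too large by factor | True type I error (nominal 5%) |
|---|---|---|
| 0.05 | 1.03 | 4.3% |
| 0.10 | 1.05 | 3.6% |
| 0.20 | 1.12 | 2.4% |
| 0.30 | 1.20 | 1.4% |

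The strata-adjusted test stays at about 5%.

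**3. Baseline adjustment, arm volume.** ANCOVA multiplies the residual variance by (1 − ρ²), so λ = 11.52 / (1 − ρ²), with 104 error degrees of freedom. The unadjusted SE of a pairwise difference is 25 × √(2/36) = 5.89.

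| ρ | 1 − ρ² | λ | SE of difference | Power |
|---|---|---|---|---|
| none (unadjusted) | 1 | 11.52 | 5.89 | 85.9% |
| 0.3 | 0.91 | 12.66 | 5.62 | 89% |
| 0.5 | 0.75 | 15.36 | 5.10 | 94% |
| 0.7 | 0.51 | 22.59 | 4.21 | 99% |

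**4. Baseline adjustment, Lymph-ICF, three groups.** The Statistical analyses section applies the one-way ANOVA to quality of life as well. With assumed means 0/7.5/15 and SD 22:

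λ = 36 × (56.25 + 0 + 56.25) / 484 = 8.37, power 72.5%.

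At ρ = 0.5, λ = 8.37 / 0.75 = 11.16 and power is 84.7%. At ρ = 0.6, λ = 8.37 / 0.64 = 13.07 and power is 90.1%.

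**5. Change or week-12 value.** Without a covariate the choice matters. The variance of a change score is 2(1 − ρ) times that of the week-12 value, so change is less precise when ρ is below 0.5 and more precise above it. If SD 25 refers to the week-12 value, arm-volume power on change is 72% at ρ = 0.3, 86% at 0.5 and 98% at 0.7. With baseline B as a covariate the choice no longer matters. The model Y − B = a + τT + bB rearranges to Y = a + τT + (1 + b)B, with the same treatment effect τ and the same standard error. This holds for a simple difference on one scale.

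**The case against.** The case on the other side is substantial, and much of it stands.

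- **The plan does adjust for the strata.** The sentence after the ANOVA adjusts for exactly the two stratification factors. A reader might infer that the plan ignores them. It does not: only the test named as primary leaves them out, and the article does not say which result leads.
- **Baseline may enter through a change score.** The abstract's definition would bring it in. That is a fair reading, but the Statistical analyses section compares groups at week 12 and names change scores only for sleep, self-efficacy and adherence. The disagreement itself needs settling.
- **There is no shortfall in power.** Step 1 confirms this. The error is also in the safe direction: the randomized comparison stays unbiased and false positives are not increased.

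Two stronger readings are tempting and should not be drawn.

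- **Very low power or near-zero type I error.** If the 20% and SD 25 are read as relative change, baseline excess is taken as uniform over 10-40% and severity is cut at 20%, simulation gives about 37% power unadjusted against about 80% adjusted, with null rejection below 1%. This rests on one outcome model that the article does not state. The unadjusted SE of 2.4 in that model implies an SD of 2.4 / √(2/36) = 10.2, not the stated 25. Most of the fall to 37% therefore comes from the changed outcome scale, not from omitted covariates.
- **A complete-case analysis that breaks intention to treat.** The article specifies no complete-case rule. Its Blinding section keeps women in their randomized group and invites those who withdraw to attend follow-up. Handling of missing values is commonly left to the full protocol or SAP. With complete data, adding week 6 in an unstructured repeated-measures model leaves the week-12 contrast unchanged.

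**Conclusion.** The concern holds in a limited form. The primary test is unadjusted despite stratified allocation, no stated model of a primary outcome contains its baseline value, the status of the adjusted models is open, and the abstract and the Statistical analyses section disagree on whether change or the week-12 value is analysed.

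The consequence is a conservative test and forgone precision, not bias or an underpowered trial. For strata the size is a type I error between about 4% and 1%, if R² lies between 0.05 and 0.30. For baseline it is a gain of about 3 to 13 points of arm-volume power for ρ from 0.3 to 0.7 (85.9% to 89-99%), taking the stated difference and SD at face value. For the three-group Lymph-ICF test it is about 12 to 18 points for ρ of 0.5 to 0.6. The article gives neither ρ nor R², and the restricted entry range for excess volume may lower ρ for that outcome, so the exact gain cannot be fixed.

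**What to change.** In the Statistical analyses section:

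1. Make the primary analysis of each outcome a linear model (ANCOVA) of the week-12 value on treatment, the baseline value of that outcome, centre and severity category.
2. Reconcile the abstract with this section on change versus week-12 value, on one named scale for arm volume. With baseline as a covariate, either choice gives the same treatment effect.
3. Keep the unadjusted one-way ANOVA as a sensitivity analysis, and state that the subgroup models are secondary.

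A repeated-measures version that uses week 6 is optional, and helps only if week-12 values are missing.

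The cost is wording only. Baseline, centre and severity are already collected and the sample size need not change. The wording should be settled before the week-12 data are analysed.
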